##### Bias control

2.2.2.5.

To control bias as much as possible, blinding techniques were adopted for data measurement and analysis, i.e., after the imaging data from each center were summarized into research groups, the grouping of clinical data was blinded to the data measurers; at the same time, a consistency test was conducted on the basic situation of the cohort composition within each center (in the same manner as study protocol 2.2.1) to control bias caused by differences in sample composition at different centers.

##### Statistical analysis

2.2.2.6.

Fisher's precision probability test was used to compare the difference between the sexes and affected sides, using analysis of variance to compare the different ages between the surgical and non-surgical cohorts. Differences in acetabular index was compared using Student's *t*-test. Chi-square test was used to compare IHDI classification, VAS and HHS, and Severin classification at the final follow-up, and analysis of variance was used to compare the MRI T1ρ mapping values and the incidence of Grade III and Grade IV adverse events.

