##### Exclusion criteria

2.2.1.2.

1.Neuromuscular or syndromic DDH;2.Repeated surgical treatment because of re-dislocation, RAD, or other reason after DDH reduction;3.Incomplete imaging data.

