##### Statistical analysis

2.2.1.4.

Statistical analysis was performed using SPSS 27.0 software (IBM, SPSS Inc.).
1.To ensure consistency and reliability between multicenter research samples, it is first necessary to conduct a consistency analysis on the structural data, such as age and sex, of the included cases from each center and the International Hip Dysplasia Institute (IHDI) classification using the Cohen's kappa statistic. Simultaneously, the baseline characteristics (such as structural composition and pathological severity) of the included cohorts within each center must be consistent; imbalances in baseline characteristics were corrected by increasing the sample size.2.The included patients were divided into the non-limbus inversion group (A) and the limbus inversion group based on the presence of limbus inversion at closed reduction. The limbus inversion group was then further divided into the RLI group (B) and the resolved inverted limbus group (C) according to the state at final follow-up. A combination consisting of any two of the groups was organized into cohorts. Fisher's precision probability test was used to compare the difference between the sexes and affected sides, using analysis of variance to compare the different ages between the two groups. Differences in acetabular index was compared using Student's *t*-test. Chi-square test was used to compare IHDI classification, VAS and HHS, and Severin classification at the final follow-up, and analysis of variance was used to compare the MRI T1ρ mapping values and the difference in the initial magnitude of limbus inversion between groups B and C, as well as the difference between the initial magnitude of limbus inversion and that at the final follow-up in group B.3.ROC curve analysis was used to predict the cut-off value of the initial magnitude of limbus inversion in the case of persistent RLI as well as calculate its specificity, sensitivity, and statistical significance.4.Sample size calculation.In this study, ossification of the acetabular cartilage was the main observation; thus, improvement of the acetabular index was the most suitable observation indicator. The sample size calculation was based on the previously published acetabular index at the final follow-up in the group with RLI and the group without RLI after closed reduction (21.41°±3.61° and 18.88 ° ± 4.32° in the two groups, respectively) (15). The significance level *α*, the statistical power of the test, the ratio of the sample sizes in the two groups, and the percentage of patients lost to follow-up were set at 0.05, 0.9, 1:1, and 20%, respectively. The minimum sample size for each group was calculated to be 67 cases (134 cases in total). Therefore, at least 67 cases needed to be enrolled in the observation group and the control group, respectively.

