##### Randomized blocks and interventions

2.2.2.2.

A randomized trial study design was the most appropriate approach to observe the efficacy of surgical intervention, with blinding techniques used during statistical analysis of the data. A double-blind study was not feasible because the surgeon was required to provide detailed information on the surgical regimen. The researchers in each center divided the RLI participants into two study cohorts based on the randomized block design, i.e., the surgery and non-surgery groups. After informed consent was obtained from the guardians of patients in the surgery group, clearance of the inverted limbus *via* arthrotomy was performed.

All surgeries were performed by pediatric hip joint surgeons with senior job titles *via* a bikini incision, and the inverted limbus tissue embedded between the acetabulum and femoral head was excised after arthrotomy without damaging the limbus-cartilage complex. After surgery, casts or braces were applied to immobilize single hips in abduction for 4 weeks and the patients gradually resumed walking after removal of external fixators. No special rehabilitation therapy was administered.

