##### Statistical analysis

2.2.3.4.

Fisher's precision probability test was used to compare the difference between the sexes and affected sides, using analysis of variance to compare the different ages between the surgical and non-surgical cohorts. Differences in acetabular index was compared using Student's *t*-test. The chi-square test was used to compare IHDI classification, VAS and HHS, and Severin classification at the final follow-up, and analysis of variance was used to compare the MRI T1ρ mapping values, re-dislocation rate, incidence of RAD, and incidence of AVN between the two cohorts.

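### Outcomes are measured per hip and bilateral children are eligible, but the unit of analysis is undefined and every named test assumes independent observations, so error rates are wrong if both hips of a child enter

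*Protocol article*

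**What the plan says.** Section 2.3.1 lists four primary outcomes: improvement in acetabular index, Severin class, magnitude of limbus inversion, and avascular necrosis of the femoral head. Each is read from one hip.

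The exclusions for part 1 (section 2.2.1.2) are "1.Neuromuscular or syndromic DDH;2.Repeated surgical treatment because of re-dislocation, RAD, or other reason after DDH reduction;3.Incomplete imaging data". Part 2 reuses them and adds refusal (2.2.2.1.2); part 3 reuses them as they stand (2.2.3.1). Bilateral disease is not mentioned.

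In part 2 (section 2.2.2.2) the allocated unit is the participant: "The researchers in each center divided the RLI participants into two study cohorts based on the randomized block design". After surgery, "casts or braces were applied to immobilize single hips in abduction for 4 weeks".

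The analysis sections of all three parts (2.2.1.4, 2.2.2.6, 2.2.3.4) name the same tests. For baseline, "Fisher's precision probability test was used to compare the difference between the sexes and affected sides". For the main outcome, "Differences in acetabular index was compared using Student's" t-test. Chi-square is named for Severin class, and analysis of variance for the T1ρ values. No paired or clustered method appears, and no rule for a child with two eligible hips.

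Part 1 alone has a sample size (2.2.1.4). Its inputs are "21.41°±3.61° and 18.88 ° ± 4.32° in the two groups, respectively", and the significance level, power, allocation ratio and loss "were set at 0.05, 0.9, 1:1, and 20%, respectively". The result is "The minimum sample size for each group was calculated to be 67 cases (134 cases in total". A case is not defined.

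**The concern.** Two hips of one child share genes, age, treatment history, surgeon and centre, so their outcomes are likely to be correlated. Student's t, chi-square, Fisher's exact test and ordinary analysis of variance all treat each record as independent. If a child supplies two records, the standard error is wrong, and so are the p-value and confidence interval.

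The grouping rules make the gap more than a matter of wording. In part 1, groups A, B and C are set by limbus state at reduction and at final follow-up. In part 3, the cohorts are set by whether inversion exceeds the cut-off. Both are features of a hip, yet the text sorts patients. A bilateral child whose hips differ would belong to two groups at once, and the article does not say what happens then. In part 2, a child with two eligible hips has one allocation and two values of every primary outcome.

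At stake are the false-positive rate of the randomised comparison, the precision reported in all three parts, and the meaning of the part 1 sample size.

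**Working it through.** **1. Reproduce the plan's figure (section 2.2.1.4).**
- Difference: 21.41 − 18.88 = 2.53°.
- Pooled SD: √[(3.61² + 4.32²)/2] = 3.981°.
- Two-sided α = 0.05 (the article does not state sidedness; two-sided reproduces its result), power 0.90, ratio 1:1.
- n per group = 2 × [3.981 × (1.960 + 1.282)/2.53]² = 52.03, rounded up to 53.
- Allowing for 20% loss: 53/0.8 = 66.25, rounded up to 67. This matches exactly.

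The stated number therefore contains no allowance for within-child correlation. At 53 independent observations per group the power is 90.5% (normal approximation).

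**2. Assumptions that the documents do not supply.**
- b, the share of children contributing two *eligible* hips: 10–40%.
- ICC, the within-child correlation of the outcome: 0.3–0.8.

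**3. Formulas.**
- The share of hips that come from two-hip children is 2b/(1+b).
- Both hips in the same group: design effect DE = 1 + ICC × 2b/(1+b).
- Hips in opposite groups: DE = 1 − ICC × 2b/(1+b).
- Actual two-sided error of the plain test = 2 × [1 − Φ(1.96/√DE)].
- Power of a valid test at 53 hips per group = Φ(3.272/√DE − 1.96), where 3.272 = 2.53/(3.981 × √(2/53)).
- Hips needed per group = 52.03 × DE, rounded up, then divided by 0.8 and rounded up.

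**4. Both hips in the same group.**

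| b | ICC | DE | Actual α | Power, 53 hips | Hips needed | After 20% loss |
|---|---|---|---|---|---|---|
| 10% | 0.3 | 1.055 | 5.6% | 89.0% | 55 | 69 |
| 20% | 0.5 | 1.167 | 7.0% | 85.7% | 61 | 77 |
| 40% | 0.7 | 1.400 | 9.8% | 79.0% | 73 | 92 |
| 40% | 0.8 | 1.457 | 10.4% | 77.3% | 76 | 95 |

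The last three columns use the part 1 inputs and apply only if cases are hips.

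**5. Every two-hip child split between groups.**

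| b | ICC | DE | Actual α |
|---|---|---|---|
| 10% | 0.3 | 0.945 | 4.4% |
| 20% | 0.5 | 0.833 | 3.2% |
| 40% | 0.7 | 0.600 | 1.1% |

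**6. Check by simulation** (20,000 t-tests under no effect, 53 hips per group). Same group: 6.8% at b = 20%, ICC 0.5, and 9.6% at b = 40%, ICC 0.7. Opposite groups: 3.4% and 1.2%. The formulas hold.

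**7. One record per child.** DE = 1 and there is no error.

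**The case against.** The strongest reply is that nothing says two hips of one child will be entered. The text speaks of patients and participants, and immobilising single hips may simply mean one operated hip per child. That phrase concerns immobilisation, so it does not establish that a child has only one operated hip or two. A condensed article may also leave an index-hip rule to the full protocol. This stands as far as it goes: the fault is conditional. But the article does not leave the analysis open. It names the test for each outcome in all three parts, and those tests suit only one of the two possible units.

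A reader might infer that type I error is inflated throughout. The documents do not support that. Inflation needs both hips in the same group, which only part 2's allocation of participants implies. In parts 1 and 3 a child's hips can fall in opposite groups, and the plain test then errs on the conservative side. With a mixture, the net direction is unknown.

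A reader might also infer that 67 per group is too few. That follows only if cases are hips. The 67 is, moreover, a minimum given for part 1; section 2.2.2 states no sample size, so the power figures do not describe the randomised part.

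The size is uncertain too. The formula needs children with two eligible hips, who cannot outnumber bilateral children. In part 2 both hips would have to meet the inversion and acetabular index limits, so the upper end of the range is an extreme.

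Finally, the Fisher sentence is a baseline comparison. The sentence on Student's t-test carries the point for the outcomes.

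**Conclusion.** The point holds in conditional form. The outcomes belong to hips, bilateral children are eligible, the unit of analysis is undefined, and the fixed tests are invalid if both hips of a child enter.

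- **Part 2, both hips in one arm:** the nominal 5% becomes about 5.6% to 10%, and 7.0% at b = 20% and ICC 0.5.
- **Parts 1 and 3:** error is inflated for hips in the same group and conservative for hips in opposite groups, at 1.1% to 4.4% if every two-hip child is split (b 10–40%, ICC 0.3–0.7).
- **Part 1 sample size:** 90% power holds only if the 67 counts children or independent hips. If it counts hips, some from the same child and in the same group, power lies between about 89% and 77%.

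All of these sizes rest on an assumed share of two-hip children and an assumed ICC; with few such children the effect is small. The documents do not show that error is inflated in all three parts, or that the sample size is deficient as it stands.

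**What to change.** 1. State in section 2.2.2.2 that the child is the unit of randomisation and that, where both hips are eligible, both belong to the same arm. Allocation by participant already points this way; the rule for two eligible hips is what is missing.
2. In sections 2.2.1.4, 2.2.2.6 and 2.2.3.4, choose one of two analyses:
   - analyse hips with a mixed model or GEE clustered on child, in place of the t and chi-square tests, using logistic or ordinal forms for avascular necrosis and Severin class. In parts 1 and 3, group can then enter as a hip-level factor, which accommodates a child whose hips fall in different groups; or
   - analyse one index hip per child, chosen by a rule fixed in advance. The named tests then no longer break independence within a child.
3. Count child-level features such as sex and age once per child, and say how a bilateral child is coded for affected side.
4. State that the 67 per group counts children. If it counts hips, restate the power with an explicit design effect.

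The cost is mostly wording. Confidence intervals become slightly wider where both hips share a group. An index-hip rule gives up the second hip's data. If the 67 was meant as hips, either recruitment rises or lower power is accepted.

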###### Inclusion criteria

2.2.2.1.1.

Inclusion criteria 1–5 are the same as the previously listed inclusion criteria 1–5 (2.2.1.1);

6. More than 1 year after closed reduction;7. Patients aged ≤5 years at follow-up;8. The magnitude of limbus inversion exceeded 32% of the horizontal depth of acetabular roof at follow-up (or the cut-off value obtained in Protocol 2.2.1);9. The acetabular index was ≤30° at follow-up (since an acetabular index>30° usually necessitates pelvic osteotomy).

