###### Exclusion criteria

2.2.2.1.2.

Exclusion criteria 1–3 are the same as previously listed exclusion criteria 1–3 (2.2.1.2);
4. Patients who refused inclusion in the study cohorts.For pediatric patients satisfying the inclusion/exclusion criteria, the basic measures of acetabular development including the acetabular index and central-edge angle were assessed using frontal pelvic radiographs; the magnitude of limbus inversion, cartilaginous acetabular index, and T1ρ mapping values were measured using MRI.

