#### Primary outcome measures

2.3.1.

1.The improvement of the acetabular index2.Severin classification3.The magnitude of limbus inversion4.Avascular necrosis (AVN) of the femoral head was assessed based on the Kalamchi–MacEwen criteria.

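### The randomised comparison of the acetabular index uses a plain t-test with no entry-value or centre term, and so loses precision that the collected data could supply

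*Protocol article*

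**What the plan says.** Section 2.2.2.6 gives the analysis of the randomised part: "Differences in acetabular index was compared using Student's" t-test, with no covariate, stratum or block term.

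The information that such terms would need is already collected:

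- **Entry index.** Section 2.2.2.1.2 says that for eligible children "the basic measures of acetabular development including the acetabular index and central-edge angle were assessed using frontal pelvic radiographs". The index is also an entry criterion in Section 2.2.2.1.1: "The acetabular index was ≤30° at follow-up".
- **Allocation.** Section 2.2.2.2 says: "The researchers in each center divided the RLI participants into two study cohorts based on the randomized block design". The factor that defines a block is not named.
- **Centre.** Section 2.2.2.5 provides a consistency test on cohort composition, intended "to control bias caused by differences in sample composition at different centers". It adds no centre term to the outcome comparison.

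Two places bear on what the t-test compares. Section 2.3.1 lists as the first primary outcome "The improvement of the acetabular index", which suggests a change. The only sizing, in Section 2.2.1.4 for the retrospective part, uses values at one time: "The sample size calculation was based on the previously published acetabular index at the final follow-up", namely "21.41°±3.61° and 18.88 ° ± 4.32° in the two groups, respectively".

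**The concern.** This is the comparison of the first-listed primary outcome in the only randomised part of the programme, where children are allocated to arthrotomy or to no surgery. That part states no sample size of its own, so nothing in the article shows that its precision is adequate.

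A two-sample t-test cannot carry a covariate or a stratum. If the entry index predicts the later index, the predictable share of the variation stays in the error term. If the outcome differs between centres and the arms are balanced within centres, the between-centre variation also stays in the error term, although the design has removed it from the treatment contrast. Both make the confidence interval wider than it needs to be.

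**Working it through.** **Inputs from the article (Section 2.2.1.4).** Means 21.41 and 18.88, SDs 3.61 and 4.32, α 0.05, power 0.90, ratio 1:1, loss 20%.

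**Inputs assumed.** The article gives neither the correlation ρ between entry and outcome index nor the intraclass correlation (ICC) for centre. I take ρ from 0.3 to 0.7 and ICC from 0.01 to 0.10, with 0.20 as a larger value. The randomised part has no stated size, so I borrow the difference, SD and analysed number from part 2.2.1 purely as an illustration.

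**Step 1: reproduce the plan's own figure.**
- Difference: 21.41 − 18.88 = 2.53.
- SD: √[(3.61² + 4.32²)/2] = 3.98.
- n per group = 2 × [3.98 × (1.960 + 1.282)/2.53]² = 52.03, rounded up to 53.
- Allowing for loss: 53/0.8 = 66.25, rounded up to 67.

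This matches the stated 67 per group. The stated size is therefore that of an unadjusted two-sided comparison of final values.

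**Step 2: variance under the two readings.** With equal variances σ² at entry and outcome, the variance per child is:
- final value: σ²
- change from entry: 2(1 − ρ)σ²
- adjusted for the entry index: (1 − ρ²)σ²

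The adjusted analysis thus has 1 − ρ² times the variance of final values, and (1 − ρ²)/[2(1 − ρ)] = (1 + ρ)/2 times the variance of change scores. Neither ratio exceeds 1. The ranking does not need equal variances. A final-value test fixes the slope on the entry index at 0 and a change-score test fixes it at 1, while the model estimates it, at the cost of one degree of freedom.

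**Step 3: numbers.** 53 analysed per arm, difference 2.53, SD 3.98, normal approximation. SE = per-child SD × √(2/53). N is per arm for 90% power after 20% loss.

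| Analysis | ρ | SE | Power | N |
|---|---|---|---|---|
| t-test, final value | any | 0.773 | 90.5% | 67 |
| t-test, change | 0.3 | 0.915 | 79.0% | 92 |
| t-test, change | 0.5 | 0.773 | 90.5% | 67 |
| t-test, change | 0.7 | 0.599 | 98.8% | 40 |
| Adjusted for entry index | 0.3 | 0.738 | 92.9% | 60 |
| Adjusted for entry index | 0.5 | 0.670 | 96.5% | 50 |
| Adjusted for entry index | 0.7 | 0.552 | 99.6% | 34 |

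Adjustment lowers the SE by about 5%, 13% and 29% against final values, and by about 19%, 13% and 8% against change scores, at ρ of 0.3, 0.5 and 0.7. Below ρ = 0.5 a change score is less precise than the final value alone.

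**Step 4: centre alone.** With the arms balanced within centre, the unadjusted SE is too large by the factor 1/√(1 − ICC). The actual two-sided level is 2[1 − Φ(1.96/√(1 − ICC))].

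| ICC | SE too large by | Actual level | Power, unadjusted | Power, adjusted |
|---|---|---|---|---|
| 0.01 | 0.5% | 4.9% | 90.6% | 90.8% |
| 0.05 | 2.6% | 4.4% | 91.1% | 91.9% |
| 0.10 | 5.4% | 3.9% | 91.7% | 93.2% |
| 0.20 | 11.8% | 2.8% | 92.9% | 95.5% |

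Up to an ICC of 0.10 the gain in power is at most 1.5 percentage points.

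**The case against.** The strongest reply is that the t-test is valid and that covariates are commonly left to an analysis plan. Section 4.2 mentions such a plan, and it is not shown. The first half stands: nothing here is biased. The second half does not remove the point. The article does not leave the method open; it fixes a test that has no place for a covariate.

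Four stronger readings are tempting, and the article does not support them.

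- **That the entry index is ignored altogether.** The primary outcome is worded as an improvement. If the t-test is on change, the entry index is used, only inefficiently.
- **That the 5% level is breached.** With balance within centres the error is in the safe direction: the actual level is below 5%, and the false-positive risk does not rise.
- **That centre is known to be the blocking factor and that institutional raters inflate the differences between centres.** Blocks are formed in each centre, but their defining factor is not named. Section 2.2.1.3 places two raters in each institution, whereas Section 2.2.2.5, written for the randomised part, describes images gathered from the centres and measured blind to group. The rater argument should not be used.
- **That a definite amount of power is lost.** The randomised part states no size, and ρ and ICC are not given. The 30° cap on the entry index narrows its range and may lower ρ, which would shrink the gain against a final-value test.

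**Conclusion.** The point holds as one of efficiency. Whichever outcome is meant, the stated t-test is less precise than a linear model that adjusts for an index already measured in every child. The size of the loss depends on ρ: an SE reduction of about 5% to 29% against final values, or 19% to 8% against change scores, over ρ 0.3 to 0.7. The centre term matters less. It restores a level that would otherwise be about 4.9% to 4% for ICC 0.01 to 0.10, and it adds little power unless the ICC is larger.

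The power figures illustrate the effect with numbers borrowed from part 2.2.1; they do not estimate the power of the randomised part. The change is worth making because it is nearly free, but a result from the t-test would not be invalid without it.

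**What to change.** In Section 2.2.2.6, replace the t-test for the acetabular index by a linear model of the index at the stated analysis time on arm, entry acetabular index and centre, plus any other factor used to form the blocks. Age at randomisation is an optional addition. Report the adjusted difference between arms with its 95% interval.

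State in the same place whether the outcome is the final value or the change from entry. With the entry index in the model, both give the same estimated difference between arms, so the choice affects only the presentation. Name the factor that defines the blocks in Section 2.2.2.2, so that the model can match the design.

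The cost is wording only. The entry index and centre are already recorded, and no further visit, image or child is needed. The change is best made before the arms are first compared at a two-yearly data pooling (Section 2.2.2.3).

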##### Cohort follow-up

2.2.1.3.

The frontal pelvic radiographs in a standing position and MRI images of the hip joints with the lower limbs in a neutral position were taken during follow-up, and the function examination and measurements were as:
1.Visual analogue scale (VAS) and Harris hip score (HHS) was used to evaluate hip joint function. As preschool children cannot describe pain precisely, we decide to change our measurements according to your recommendation. For preschoolers who are unable to describe their specific situation, along with Harris hip score, a visual analogue scale (VAS) was also applied for the assessment of pain severity of participants (17). In order to determine VAS score, a 100-mm horizontal line without scaling was designed in which 0 was marked as “no pain in hip” and 10 was marked as “unbearable pain”. Participants were then instructed to place a vertical mark reflecting their soreness severity.2.The acetabular index, Sharp's angle, cartilaginous acetabular index, and central-edge angle were measured using frontal pelvic radiographs; the morphology of the hip joints was evaluated using the Severin classification.3.The presence of RLI was observed on T2-weighted fat-suppressed MRI sequences of the hip joints. If RLI was present, the magnitude of limbus inversion was measured at level with the center of the triangular cartilage (16) (Figure 3, schematic diagram of MRI limbus inversion degree measurement).4.MRI T1ρ mapping.

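### VAS and HHS, described as scores, are assigned a chi-square test in all three parts; a rank test with an estimated difference fits them better

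*Protocol article*

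**What the plan says.** The three statistical sections use nearly the same sentence. Sections 2.2.1.4 (item 2) and 2.2.2.6 read "Chi-square test was used to compare IHDI classification, VAS and HHS", followed by the Severin classification at the final follow-up. Section 2.2.3.4 reads "The chi-square test was used to compare IHDI classification, VAS and HHS, and Severin classification at the final follow-up".

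The two measures are described in section 2.2.1.3, item 1: "Visual analogue scale (VAS) and Harris hip score (HHS) was used to evaluate hip joint function". For the VAS, "a 100-mm horizontal line without scaling was designed", with end anchors 0 and 10, and the participant places a mark on it. The HHS is called a score. The article gives no grades, bands or cut-offs for either one.

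Other numeric measures in the same paragraphs get methods for numeric data. For the acetabular index, "Differences in acetabular index was compared using Student's *t*-test"; age and the T1ρ values get analysis of variance. Section 2.3.2 lists VAS and HHS as secondary outcomes.

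**The concern.** Pearson chi-square compares counts across unordered categories. It suits IHDI, which is a classification. Applied to a score, it treats 20 and 21 as being as different as 20 and 90, and it does not use the direction of a shift. It returns a p-value but no difference with an interval.

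As the article stands, the test could be run in two ways. With every observed value as its own category, most expected counts are too small for the chi-square approximation. With scores grouped first, the result depends on a grouping that the article does not state.

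VAS and HHS are the only pain and function measures among the listed outcomes; the rest are imaging measures. Part 2 randomizes children to arthrotomy or no surgery, so readers will want to know how large any difference in pain or function is, in either direction. The named test answers that poorly.

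**Working it through.** **1. Test against type of variable (sections 2.2.1.3 and 2.2.2.6)**

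| Measure | Described as | Test named |
|---|---|---|
| Acetabular index | angle | Student's t |
| Age, T1ρ values | numeric | analysis of variance |
| IHDI, Severin | classification | chi-square |
| VAS | mark on a 100-mm line | chi-square |
| HHS | score | chi-square |

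VAS and HHS are the only scores placed with the classifications.

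**2. Number of evaluable patients.** The only sample size is in section 2.2.1.4, for part 1 and the acetabular index: 21.41 ± 3.61 against 18.88 ± 4.32, alpha 0.05 (taken as two-sided), power 0.9, 20% loss.

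- Difference: 21.41 − 18.88 = 2.53.
- Common SD: √[(3.61² + 4.32²)/2] = 3.98. Standardized difference: 2.53/3.98 = 0.636.
- n = 2 × [3.98 × (1.960 + 1.282)/2.53]² = 52.03, rounded up to 53 per group.
- Allowing for loss: 53/0.8 = 66.25, rounded up to 67.

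This reproduces the stated 67 per group, so the sample size is not in question. The evaluable number behind it is 53. Parts 2 and 3 state no size, so using 53 there is an assumption.

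**3. Sparseness on ungrouped values.** With two equal groups of 53 (106 in total), an expected count of 5 per cell needs each distinct value to occur at least 10 times. Since 106/10 = 10.6, at most 10 distinct values can meet this. A mark on a 100-mm line read in whole millimetres can take 101 values.

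**4. Illustrated power, normal scores.** Assumptions: scores on 0–100, mean 50, SD 15, rounded to whole numbers; 53 per group; two-sided 0.05; 3000 simulated trials per row. Entries are the percentage of trials that reject.

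| Shift (SD) | t | Rank-sum | Chi-square, median split | 4 groups | 11 levels | Raw values |
|---|---|---|---|---|---|---|
| 0 | 5.9 | 5.7 | 4.7 | 5.4 | 3.4 | 0.5 |
| 0.3 | 35 | 34 | 22 | 19 | 11 | 0.7 |
| 0.5 | 71 | 70 | 52 | 47 | 27 | 1.2 |
| 0.636 | 91 | 89 | 72 | 71 | 49 | 1.7 |
| 0.8 | 98 | 98 | 89 | 90 | 74 | 3.3 |

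Near 70%, simulation error is about ±1.96 × √(0.7 × 0.3/3000) = ±1.6 points. Separate runs of the 0.5 SD case put the t and rank tests between about 70% and 74%.

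**5. Illustrated power, scores near a ceiling.** Both cases use 53 per group.

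- Mean 92, SD 8, capped at 100, shift 0.5 SD: t 71%, rank-sum 70%, chi-square on four assumed grades (cuts 70, 80, 90) 44%, on raw values 11%. With no shift, chi-square on raw values rejects in 1.7%.
- Skewed scores, 100 minus a gamma variable (shape 2, scale 5; SD = 5 × √2 = 7.07), 3-point downward shift (3/7.07 = 0.42 SD): rank-sum about 71%, chi-square about 30% on four bands (cuts 70, 80, 90), about 61% when rounded to the nearest ten, about 16% on raw values.

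**The case against.** The strongest reply is that the article condenses a fuller protocol. VAS and HHS stand between two classifications in the sentence, which is compatible with graded scores. Chi-square is admissible on grouped scores, and score bands are a detail an article may leave out. This has weight: the article does not show that the bands will be chosen after the data are seen. A reader might infer that cut points could be picked to steer the result. Nothing in the text says so, and sections 2.2.2.2 and 2.2.2.5 describe blinded measurement and analysis. The reply does not rescue the test, because Pearson chi-square ignores the order of graded scores as well.

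A reader might also take the 1% figure as the expected power. It holds only if every whole number is its own category. The VAS anchors of 0 and 10 would also allow an 11-level reading, which gives 27% at 0.5 SD.

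The loss also depends strongly on the grouping. In the skewed case at 67 per group, rounding to the nearest ten gave about 75% power, against 70% for the t-test and 84% for the rank test. So chi-square does not lose to every alternative under every grouping. It fell below the rank test in each case with a true shift that was tried.

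Finally, these are secondary outcomes for which the article claims no power. At a 0.3 SD shift even the t-test reaches only about 35%, so a missed small effect would not be due to chi-square alone.

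**Conclusion.** The point holds as a mismatch between a named test and the variables the article describes, repeated in all three parts. It is a stated choice and not an omitted detail, and it needs no simulation to establish.

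The size of the loss is illustrative. At 53 evaluable per group, chi-square on grouped values gives roughly 27–52% power where a t or rank test gives 70–74% (normal scores, 0.5 SD). For the skewed scores it gives 30–61% where the rank test gives about 71%. On raw values it gives about 1% and 16% in these two cases, with a type I error of 0.5% to 1.7% in the null cases run. Distributions, shifts, groupings and the HHS range of 0–100 are assumptions, as is carrying part 1's number to parts 2 and 3.

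A reader might infer that the trial is too small. The documents do not support that: the 67 per group reproduces and rests on the acetabular index. The change should be made, but the primary comparisons do not depend on it.

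**What to change.** In sections 2.2.1.4, 2.2.2.6 and 2.2.3.4, take VAS and HHS out of the chi-square sentence. Compare them with the Wilcoxon rank-sum test and report the Hodges-Lehmann difference with a 95% interval. Part 1 compares its three groups in pairs, so the same two-group method serves there. A rank test is preferable to the t-test because these scores may crowd at one end of the scale. Keep chi-square or Fisher's exact test for IHDI.

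If graded scores are intended, state the grades in advance and use a test that respects their order, such as the rank-sum test with ties or a trend test.

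The cost is protocol wording only: no new data, visits or patients, and no change to the stated sample size. The same edit could correct the reverse mismatch in sections 2.2.2.6 and 2.2.3.4, where analysis of variance is named for incidences (adverse events; re-dislocation, RAD and AVN).
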